##### Neuroimaging

MRI will be performed on a 3.0 T Phillips Ingenia wide-bore MR scanner (70 cm bore size) fitted with an 8-channel, phased-array receive-only head coil. T1- and T2-weighted images will be acquired for radiologic assessment and image registration. We want to explore voxel-wise structural and functional changes associated with participation in the different treatments across the brain and in functionally-defined brain regions of interest relating to meta-awareness, body awareness, memory consolidation-reconsolidation, and emotion regulation. The main ROI for structural and functional datasets are defined as primary and secondary somatosensory cortices, anterior cingulate cortex, thalamus, insula, amygdala, hippocampus, frontal pole and orbitofrontal cortex. These ROI will be delineated with the aid of a neuroimaging atlas such as the WFU Pickatlas [81]. Prior to and after MRI, all participants will be asked to rate perceived pain intensity using a horizontal visual analog scale (100 mm length) marked “no pain” and “maximum pain” at the endpoints. The time frame is “the day of responding” and “during the MRI session”, respectively.

##### Brain structure

Our intention is to use longitudinal *voxel-based morphometry* (VBM), an automated structural MRI analysis technique, to examine whether the three interventions (TAU, TAU + MBSR, TAU + FibroQoL) produce local changes in grey matter. We will acquire high-resolution T1-weighted 3-dimensional volume scans pre and post treatment to assess for the presence of longitudinal change following treatment. Specifically, relative local increases and decreases between pre- and post-treatment scans will be compared within and between study groups. In addition, we will use *Diffusion tensor imaging* (DTI). The diffusion MR data will be analysed by using the diffusion tensor model. After a mathematical diagonalisation process, the eigenvectors and eigenvalues describing the tensor ellipsoid will be determined. Then, two standard diffusion indices will be obtained: the apparent diffusion coefficient and the fractional anisotropy. DTI scans pre and post treatment will permit to assess changes in axial diffusivity, with lower values being interpreted as structural enhancement of white matter. For example, lower axial diffusivity at post-treatment in MBSR participants compared to control participants would suggest a white matter increase as consequence of meditation training.

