### Participants

A total of 180 FMS patients will be recruited from the Rheumatology service at Sant Joan de Déu Hospital (St. Boi de Llobregat, Spain). Sample size is established on the basis of a previous meta-analysis of controlled MBSR trials [45] in which a mean effect size of *d* = 0.53 was found. This effect size results in 1-b = 0.89 (alpha = 0.05) for *N* = 60 patients per group (180 patients overall). With 20 % maximal attrition, the power remains 1-b = 0.82. The estimated sample size for the study of biomarkers (neuroimaging and cytokines) was 30 participants per condition, this sample size is considered adequate given that approximately 20–40 participants (in between-group designs) are necessary to detect a change of 15 % in cerebral blood flow in regions of interest (ROI) by means of pseudo-continuous Arterial Spin Labeling (pCASL) [46].

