#### Neuroimaging analyses

Treatment-related differences in both structural and functional MRI datasets will be assessed using mass-univariate voxelwise General Linear Models. Thus, repeated measures ANOVA functions available in SPSS will be computed to examine between- and within-group effects of treatments. A standard threshold of *p* < 0.05 will be applied for ROI data, correcting for multiple comparisons.

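### The DTI text lists ADC and FA as its indices but reads lower axial diffusivity, a third index, as white-matter gain; axial diffusivity alone cannot support that reading

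*Protocol article*

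**What the plan says.** In the protocol article, the DTI plan is in the Brain structure section under Study measures. It first says that "the eigenvectors and eigenvalues describing the tensor ellipsoid will be determined", and then that "two standard diffusion indices will be obtained: the apparent diffusion coefficient and the fractional anisotropy". Axial diffusivity is not among the two.

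The next sentence turns to axial diffusivity: pre- and post-treatment scans are to assess "changes in axial diffusivity, with lower values being interpreted as structural enhancement of white matter". A worked example follows, in which lower post-treatment axial diffusivity in the MBSR arm than in controls "would suggest a white matter increase as consequence of meditation training".

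No direction is given for FA or ADC, and radial diffusivity is not mentioned. The Neuroimaging analyses section does not settle the matter. It says only that "Treatment-related differences in both structural and functional MRI datasets will be assessed using mass-univariate voxelwise General Linear Models", without naming a DTI index or a favourable direction.

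**The concern.** There are two linked problems. First, the indices listed and the index interpreted differ, so a reader cannot tell which DTI quantity is the outcome. Second, the reading attached to axial diffusivity is unconditional: any fall counts as improvement, whatever the other diffusion measures from the same tensor show.

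Axial diffusivity is only the largest of three eigenvalues. FA describes how far that eigenvalue stands out from the other two. A rule that looks at the largest alone gives one verdict to patterns that differ in kind.

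At stake is what the sub-study may conclude about white matter. Pre-post change in brain structure belongs to the trial's second objective. In this section VBM is aimed at grey matter, which leaves DTI as the technique described for white matter. A report that follows the text could announce white-matter gain due to meditation while its own FA map shows a fall.

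**Working it through.** The article gives no DTI figure, so there is none to reproduce. The check uses the definitions of the indices with assumed eigenvalues (units 10^-3 mm²/s).

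**Definitions**, for eigenvalues l1 ≥ l2 ≥ l3:
- axial diffusivity AD = l1
- radial diffusivity RD = (l2 + l3)/2
- ADC, taken as mean diffusivity, m = (l1 + l2 + l3)/3
- FA = sqrt(1.5 × Σ(li − m)² / Σ li²)

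**Step 1: what governs FA.** If l2 = l3 and AD exceeds RD, the formula reduces to FA = (AD − RD)/sqrt(AD² + 2 RD²). With r = AD/RD this is (r − 1)/sqrt(r² + 2), which rises with r. So FA falls when AD falls proportionally more than RD, stays the same when both fall in proportion, and rises when RD falls proportionally more.

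**Step 2: one axial fall, four outcomes.** The baseline is (1.40, 0.50, 0.50): FA = 0.90/sqrt(1.96 + 0.50) = 0.574 and ADC = 2.40/3 = 0.800. AD then falls 10% to 1.26.

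| RD after | FA | Change in FA | ADC |
|---|---|---|---|
| 0.57 (rises) | 0.69/sqrt(1.5876 + 0.6498) = 0.461 | −20% | 0.800 |
| 0.50 (unchanged) | 0.76/sqrt(1.5876 + 0.5000) = 0.526 | −8% | 0.753 |
| 0.45 (−10%) | 0.81/sqrt(1.5876 + 0.4050) = 0.574 | none | 0.720 |
| 0.40 (−20%) | 0.86/sqrt(1.5876 + 0.3200) = 0.623 | +9% | 0.687 |

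The stated reading calls every row enhancement.

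**Step 3: other baselines.** With AD down 10% and the other two eigenvalues fixed, FA moves as follows:
- (1.5, 0.5, 0.5): 0.603 to 0.558
- (1.2, 0.6, 0.6): 0.408 to 0.349
- (1.7, 0.3, 0.3): 0.799 to 0.775
- (1.0, 0.8, 0.7): 0.181 to 0.124

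The direction is the same for anisotropic, weakly anisotropic and non-symmetric tensors.

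**Step 4: can AD be recovered from the two listed indices?** Not in general. Tensors (1.50, 0.50, 0.50) and (1.45, 0.744, 0.306) both have ADC 0.833 and FA 0.603, yet their AD differs. AD has to come from the eigenvalues, so it needs to be named as an output.

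**The case against.** The best defence is that this is loose listing. The plan determines the eigenvalues, AD is the largest of them, and the text does not say that only two indices will be produced. That stands: a reader might infer that axial diffusivity cannot be measured under this plan, and that would be wrong.

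A reader might also infer that the whole structural conclusion about MBSR hangs on axial diffusivity. The documents do not support that either. VBM is described first and compares grey-matter change within and between arms, FA and ADC are also obtained, and no endpoint or decision rule is tied to AD.

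The most tempting stronger reading is that the rule would present harm as benefit because a fall in FA is unfavourable. The article gives no direction for FA, and the tensor formulas show only that AD and FA can move apart, not which movement means better tissue. Making FA the sole arbiter would replace one fixed favourable direction with another: FA also rises when AD rises with RD unchanged (for example 0.603 to 0.641 when AD goes from 1.50 to 1.65 at RD 0.50).

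Finally, an article may leave imaging detail to a fuller document, so the absence of radial diffusivity, or of a rule for discordant maps, is not a fault in itself. What remains is what the article does state: an index list that its next sentence departs from, and an unconditional inference that the index cannot carry.

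**Conclusion.** The point holds in this form: the DTI text lists ADC and FA, interprets axial diffusivity instead, and reads any fall in it as white-matter gain, although such a fall is compatible with FA moving in either direction or not at all. In the illustration, a single 10% axial fall spans FA changes from −20% to +9%.

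The eigenvalues and the size of the shifts are assumed, so these figures show what is possible, not how likely it is. The directions rest only on the definitions, with ADC taken as mean diffusivity.

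The consequence is limited to one modality in an exploratory sub-study of 30 participants per arm, whose size was argued from cerebral blood flow by pCASL and not from any DTI index. The FIQR primary analysis and the trial's sample size are not affected. The text should still be changed before analysis, because the change alters what the sub-study may claim.

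**What to change.** - Name the DTI indices once and use the same list in the Brain structure and Neuroimaging analyses sections.
- Compute axial and radial diffusivity from the eigenvalues already planned. Test them two-sided and report them beside FA and ADC.
- Delete the statement that lower axial diffusivity by itself shows enhancement, and reword the MBSR example to match.
- Interpret white-matter change only from the joint pattern of the four indices, and report an isolated axial change as being of uncertain direction.
- Naming FA as the main DTI index is optional and not needed to repair the problem.

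The cost is two further maps from existing data, slightly more analysis, and a few sentences of text. No new scans are required. The downside for the investigators is that fewer axial-only results can be called favourable.

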##### Brain function

Recent evidence [82] has demonstrated the suitability of pseudo-continuous arterial spin labeling (pCASL), a perfusion MRI technique, to quantify changes in regional cerebral blood flow (rCBF) that relate to the experience of ongoing persistent pain. In this study we will assess rCBF prior to and following the three treatments. pCASL data acquisition, pre-processing, and analysis methodologies have been published [82, 83], as applied to various disease states and therapeutic regimens, using gold-standard software packages (SPM-8 and FSL). We will acquire pCASL images using a gradient echo single shot echoplanar imaging readout resulting in whole-brain blood-flow maps. We will analyse pre-post rCBF differences within and between groups, and whether pre-post rCBF differences are related to variability in subjective ongoing pain.

Multiple resting-state networks have been found which show activity during rest and during tasks. One of them is the DMN, which shows a decrease in activity during cognitive tasks and is activated during self-referential thinking. Napadow et al. [12] showed that resting connectivity between the insular cortex (region involved in pain perception) and the DMN is significantly correlated with clinical pain at the time of the scan in FMS patients. In this work, we will use resting-state fMRI to compare changes in insular cortex-DMN connectivity between study conditions as well as to analysing any correlation between this connectivity and clinical pain. During the 8-min resting state fMRI acquisition period, the FMS patients will be instructed to remain awake with their eyes closed.

##### Inflammatory markers

Blood samples will be collected and serum will be stored at −80° for biochemical analyses. Levels of the following inflammatory markers will be assessed: IL-6, IL-8, IL-10, and high-sensitivity C-reactive protein [84]. Milliplex® assay kits (Human High Sensitivity T Cell kit) from MerkMilliporte (commercial firm) will be used for cytokine quantification in a Luminex® platform. CRP-hs will be assessed by turbidimetry in an Olympus AU5400 Autoanalyser.

### Statistical analyses of study outcomes

SPSS v22.0, STATA v13.0 and Mplus v7.2 will be used for the statistical analyses. One-way ANOVAs (with post hoc Tukey’s HSD or Games-Howell tests) for continuous values and *χ*^2^ tests with continuity corrections for categorical values will be computed on all baseline measures and socio-demographic variables to examine pre-treatment differences between groups.

#### Analysis of clinical efficacy

To assess treatment effects, we will perform Intention-to-Treat analyses, which will include all participants who undergo random allocation, using multiple imputation to replace missing values.

To study the differences in the primary outcome and in each of the secondary outcomes between groups, linear mixed-effects models [85] will be prepared using Restricted Maximum Likelihood to estimate the parameters. Comparisons amongst treatment groups at post-treatment and at 12-month follow-up will be computed with estimates derived from the linear mixed-effect models (use of the Bonferroni method to adjust the significance level of the pairwise contrasts). Calculations of between-groups effect sizes using Cohen’s *d* with its 95 % confidence interval will be based on the pooled standard deviation at baseline. Finally, to make the findings from the present RCT meaningful to clinicians, the number-needed-to-treat (NNT) [86] in the MBSR condition will be reported. Taking the Luciano et al. [87] NNT approach as our reference, we dichotomise participants into responders or non-responders using three separate cut-off criteria: (a) ≥ 20 % reduction on the FIQR total score from baseline to post-treatment; (b) ≥ 50 % reduction on the FIQR total score from baseline to post-treatment; and (c) number of patients crossing a cut-off point (reaching no worse than mild functional impairment; FIQR total score < 39).

Given that some pharmacological treatments may interfere with cytokine levels [88], differences in cytokine levels between patients taking vs. not taking antidepressants will be evaluated.

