### Study measures

Study participants will complete the following instruments as part of a paper-and-pencil battery of measures (see Table 3):*Sociodemographic-clinical questionnaire*. The following information will be collected: gender, age, ethnic group, marital status, living arrangements, educational level, employment status, and annual income. Relevant clinical variables, such as family and personal medical history, years of FMS diagnosis and comorbid conditions will also be assessed.

**Table 3 Tab3:** Study periods at which measures and data are collected

Study measures	Baseline	During treatment	2 months	12-months
Demographic information (gender, age, etc.)	X			
History of FMS (years of illness)	X			
Contact details	X			
SCID-I (depression module)	X			
*Screening measures*				
MMSE (cognitive impairment)	X			
*Primary outcome measure*				
FIQR (functional impairment)	X		X	X
*Secondary outcome measures*				
FSDC (fibromyalginess)	X		X	X
HADS (anxiety and depression)	X		X	X
PSS-10 (perceived stress)	X		X	X
MISCI (subjective cognitive impairment)	X		X	X
EQ-5D-5L (quality of life)	X			X
CSRI (health economic evaluation)	X			X
FFMQ^a^ (mindfulness facets)	X		X	X
PCS^a^ (pain catastrophizing)	X		X	X
PIPS^a^ (psychological inflexibility)	X		X	X
SCS-12^a^ (self-compassion)	X		X	X
*Other measures*				
Structural + Functional Neuroimaging data	X		X	
Inflammatory data	X		X	
CEQ (Expectation/Satisfaction with treatment)	X (EXP)		X (SAT)	
PGIC & PSIC (Impression of change)			X	X
Treatment attendance form: Attendance at each scheduled MBSR/FibroQoL session		X		
Log of MBSR and FibroQoL practices		X		
Treatment fidelity (review of video-taped MBSR sessions) & monitoring of adverse events		X	X	X

*CEQ* Credibility/Expectancy Questionnaire, *CSRI* Client Service Receipt Inventory, *EQ-5D-5L* EuroQoL questionnaire, *FFMQ* Five Facet Mindfulness Questionnaire, *FIQR* Revised Fibromyalgia Impact Questionnaire, *FSDC* Fibromyalgia Survey Diagnostic Criteria, *HADS* Hospital Anxiety and Depression Scale, *MISCI* Multidimensional Inventory of Subjective Cognitive Impairment, *MMSE* Mini-Mental State Examination, *PCS* Pain Catastrophizing Scale, *PGIC & PSIC* Patient Global and Specific Impression of Change, respectively, *PIPS* Psychological Inflexibility in Pain Scale, *PSS-10* Perceived Stress Scale, *SCID-I* Structured Clinical Interview for DSM Axis I Disorders, *SCS-12* Self-Compassion Scale

^a^Secondary outcome measures that also considered process variables

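### The article gives baseline FIQR no role in the primary mixed-model contrasts; stating a baseline-adjusted contrast would cost nothing and could add useful power

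*Protocol article*

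**What the plan says.** In the Protocol article, Table 3 under Study measures lists the primary outcome, "FIQR (functional impairment"), at baseline, 2 months and 12 months.

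Under Analysis of clinical efficacy, for the primary and each secondary outcome, "linear mixed-effects models [85] will be prepared using Restricted Maximum Likelihood to estimate the parameters". The between-arm tests follow: "Comparisons amongst treatment groups at post-treatment and at 12-month follow-up will be computed with estimates derived from the linear mixed-effect models", with a Bonferroni adjustment of the pairwise contrasts. That section therefore fixes the model class, the estimator, the visits compared and the multiplicity rule. It does not list fixed effects or say how baseline FIQR enters.

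The article gives baseline values other uses: the standard deviation that scales Cohen's d, the percentage-reduction responder definitions, the tests of pre-treatment differences, and the change scores in the mediational analyses. None of these is an adjustment of the primary contrast.

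The sample size paragraph under Participants takes an effect from a meta-analysis, "a mean effect size of *d* = 0.53 was found", and continues: "This effect size results in 1-b = 0.89 (alpha = 0.05) for *N* = 60 patients per group". For dropout it adds: "With 20 % maximal attrition, the power remains 1-b = 0.82". It uses no correlation between visits.

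**The concern.** A mixed model does not adjust for baseline by itself. What the arm contrast at a later visit means depends on how the baseline measurement is handled, and there are three common possibilities:

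- Baseline is one of the repeated responses and each arm has its own baseline mean. With complete data, the arm difference at a later visit is then the raw difference in means, and the group-by-visit interaction is a difference in change scores.
- Baseline is left out of the model. The contrast is again the raw difference.
- Baseline is a covariate, or a response with one mean common to all arms. The contrast is then baseline-adjusted.

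Only the third uses the baseline information fully, and the article does not commit to it. The first is a common default in software. If it is used, precision is lost on the primary question, and a raw difference also carries any chance imbalance in baseline severity into the estimate. The eligibility criteria set no FIQR range, so baseline severity is not restricted at entry.

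**Working it through.** **Inputs.** From Participants: d = 0.53, alpha 0.05, 60 per arm, 20 % attrition (60 × 0.8 = 48 per arm). From Analysis of clinical efficacy: Bonferroni over the pairwise contrasts; three arms give three pairs, so 0.05/3 = 0.0167 at one visit. Assumed, because the document does not give it: the correlation ρ between baseline and follow-up FIQR, taken as 0.5 with a range of 0.3 to 0.7. Also assumed: d is standardised on the raw-score standard deviation.

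**Step 1: the plan's own figures.** Power comes from a noncentral t with 2n − 2 degrees of freedom and noncentrality d√(n/2).

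- One-sided 0.05: 0.893 at n = 60 and 0.825 (0.8245 unrounded) at n = 48. These match the stated 0.89 and 0.82.
- Two-sided 0.05: 0.821 and 0.729. These do not match.

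The stated power thus corresponds to a one-sided 0.05 test with no Bonferroni step and no baseline adjustment.

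**Step 2: variance of each contrast**, relative to the raw difference, whose variance is 2/n in SD units:

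- raw difference at a visit: 1
- change score: 2(1 − ρ)
- baseline-adjusted: 1 − ρ²

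The adjusted variance is never the largest: 1 − ρ² ≤ 1, and 2(1 − ρ) − (1 − ρ²) = (1 − ρ)² ≥ 0.

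A generalised least squares calculation with three arms, three visits, equal correlation between visits and complete data confirms this for the mixed model. With separate baseline means, the relative variance of the arm difference at a later visit is 1.00 at every ρ tried. With a common baseline mean it is 0.91, 0.75 and 0.51 at ρ = 0.3, 0.5 and 0.7, which equals 1 − ρ².

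**Step 3: power.** The effective d is 0.53 (raw), 0.53/√(2(1 − ρ)) (change) and 0.53/√(1 − ρ²) (adjusted, one degree of freedom fewer). At ρ = 0.5 the adjusted value is 0.53/√0.75 = 0.612. The change-score value is 0.53/√1 = 0.53, the same as raw.

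Two-sided 0.05/3, 60 per arm:

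| ρ | raw | change | adjusted | gain over raw (points) | gain over change (points) |
|---|---|---|---|---|---|
| 0.3 | 0.682 | 0.512 | 0.730 | 4.8 | 21.8 |
| 0.5 | 0.682 | 0.682 | 0.820 | 13.8 | 13.8 |
| 0.7 | 0.682 | 0.905 | 0.947 | 26.5 | 4.3 |

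Other settings at ρ = 0.5, where raw and change have the same power:

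| test | n per arm | raw or change | adjusted | gain (points) |
|---|---|---|---|---|
| two-sided 0.05/3 | 48 | 0.565 | 0.712 | 14.7 |
| two-sided 0.05 | 60 | 0.821 | 0.914 | 9.3 |
| two-sided 0.05 | 48 | 0.729 | 0.843 | 11.4 |
| one-sided 0.05 | 60 | 0.893 | 0.954 | 6.1 |
| one-sided 0.05 | 48 | 0.825 | 0.908 | 8.4 |

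**The case against.** The strongest reply is that the article is silent on this, not wrong. It lists no fixed effects, and its sentence about comparisons at the two later visits would equally describe a model that already adjusts for baseline. A condensed article commonly leaves model terms to a fuller plan. This reply stands in part. A reader might infer that the protocol specifies an unadjusted contrast; the text does not support that, and adjustment may already be intended.

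A reader might also take 14 points as the size of the loss. That figure needs two-sided 0.05/3, a correlation the document does not give, and a d standardised on raw scores, although the article does not say how the meta-analytic effect was standardised. At alpha 0.05, the level used in the sizing, the gain at ρ = 0.5 is about 9 to 11 points two-sided and about 6 to 8 one-sided. If baseline is already in the model, it is zero. Nor do the low starting values of 0.68 and 0.56 (0.565 at 48 per arm) come from leaving out baseline; they come from testing two-sided with Bonferroni, which is a separate matter of sizing.

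What the reply does not remove is that two common ways of fitting the described model give a less precise contrast, and the article does not choose between these and the better one.

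**Conclusion.** The point holds as a free improvement, not as an error in the plan. The document fixes the model class, the visits and the multiplicity rule for the primary comparison but gives no role to a baseline measurement it collects. Under the usual group-by-visit model with separate baseline means, the contrast would be a raw difference or a change score, and the adjusted contrast is more precise than both at every correlation checked.

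With 60 per arm, two-sided 0.05/3 and an assumed correlation of 0.5, power goes from about 0.68 to 0.82. Over correlations of 0.3 to 0.7 the gain is about 5 to 27 points against the raw difference and about 22 to 4 points against a change score. These sizes rest on the assumed correlation, on d being on the raw-score scale, and on three Bonferroni comparisons. Confidence that the planned analysis actually omits baseline is low, because the text does not say.

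**What to change.** State in the analysis section that the primary model fits the 2-month and 12-month FIQR with arm, visit, arm-by-visit, baseline FIQR and baseline-by-visit as fixed effects. The alternative is to keep baseline as a response and constrain the arm means to be equal there. Take the Bonferroni-adjusted pairwise contrasts at each visit from that model, and handle every secondary outcome measured at baseline in the same way. If a fuller plan already does this, one sentence saying so is enough.

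The cost is wording only: no extra patients, visits or data, and one or two degrees of freedom. The choice should be fixed before any unblinded analysis.
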